## Abstract

**Background:** Visual Snow (VS) syndrome is believed to be due to aberrant central visual processing. Positron Emission Tomography (PET) brain imaging and visual evoked potential studies provide evidence for excessive neuronal activity in the medial temporal lobe, specifically the lingual gyrus, and suggest the VS syndrome is a hyperexcitability syndrome. These data provide the basis for consideration of repetitive transcranial magnetic stimulation (rTMS) as a potential treatment for the VS syndrome.

**Objective:** To publish the study protocol for a pilot study underway at the University of Colorado School of Medicine to investigate the use of rTMS intervention to improve symptoms and visual dysfunction associated with VS. The study aims to determine the adverse events and drop-out rate, evaluate performance of outcome measures, including a novel VS symptom scale, and describe changes in outcomes associated with treatment.

**Methods and Design:** Up to 10 participants meeting criteria for VS syndrome, age 19–65 years, will undergo an open-label intervention consisting of 10 rTMS sessions, occurring 5 days a week over a 2-week period. Participants will complete pre-treatment and post-treatment assessments that include: the Colorado Visual Snow Scale (CVSS), the National Eye Institute Visual Functional Questionnaire—25 (VFQ-25), the General Anxiety Disorder—7 scale (GAD-7), and three psychophysical visual processing tasks.

**Discussion:** Knowledge gained from this pilot study will inform future study planning and provide valuable lessons for future investigation of rTMS for the VS syndrome. An overview of study proceedings thus far demonstrates recruitment challenges associated with the COVID-19 pandemic, and additional challenges that are unique to the VS syndrome and to treatment schedules associated with TMS.

**Registration:** This study has been approved by the Colorado Multiple Institutional Review Board. ClinicalTrials.gov Identifier: NCT04925232.

## Introduction

People with Visual Snow (VS) syndrome perceive small, moving dots, which resemble the TV static of a poorly tuned analog television, in a constant manner throughout their visual field. Other symptoms include palinopsia or visual trails, light sensitivity, excessive awareness of flashes of lights and floaters, tinnitus, and balance problems. VS most often affects young people in the third decade of life, but it can strike anyone at any age, including children and older adults (1, 2). Comorbidity includes migraine headaches, which are present in 60–80% of people with VS (2). There is no effective treatment, and the cause is unknown. Many patients with VS have difficulty with visual functions and can struggle to continue working because of the visual symptoms associated with the syndrome (2). The International Headache Society (IHS) published criteria (3) for the VS syndrome and these criteria are summarized in Table 1.

**Table 1 T1:** Summary of international headache society criteria for visual snow (3).

**Criteria A through D must be met**
A. Dynamic, continuous tiny dots in the entire visual field >3 months
B. At least two of four additional symptoms 1. Palinopsia (visual after-images, trailing of moving objects, or both) 2. Enhanced entoptic phenomena with at least one of the following: excessive floaters in both eyes, excessive blue field entoptic phenomenon, self-lighting perceived with eyes closed, or spontaneous photopsia. 3. Photophobia 4. Nyctalopia
C. Symptoms not consistent with typical migraine visual aura per International Headache Society criteria.
D. Symptoms are not better explained by another disorder (including normal ophthalmic tests and no intake of psychotropic drugs).

The objective of this manuscript is to describe the research protocol for an ongoing, open-label treatment study of repetitive transcranial magnetic stimulation (rTMS) for VS syndrome at the University of Colorado School of Medicine. The aim of this pilot study is to investigate the feasibility of a future randomized controlled trial of rTMS to improve visual function and symptoms associated with VS. Specifically, this study aims to determine: (1) adverse events and drop-out rate, (2) the standard deviation and test-retest reliability of a novel scale (Colorado Visual Snow Scale or CVSS) and performance of three psychophysical visual processing tasks previously investigated by McKendrick et al., and (3) describe changes in outcome measures (described below) following treatment with rTMS.

VS syndrome is believed to be due to aberrant central visual processing that results in excessive neuronal activity in regions of the brain that perform higher order visual processing (4). Given all findings and symptoms, some authors have posited that VS syndrome is due to thalamocortical dysrhythmia (1). Data from Positron Emission Tomography (PET) brain imaging studies and visual evoked potential studies indicate that the excessive neuronal activity occurs in the medial temporal lobes, specifically the right lingual gyrus (5). Although this evidence suggests that the lingual gyrus plays a role in VS, it is not clear whether increased metabolic activity in this region occurs as a result of upstream neuronal dysfunction or is the primary cause of VS syndrome. In either case, similar syndromes with evidence for central nervous system hyperexcitability have the potential to be treated using rTMS, such as cerebellar hyperexcitability (6), central pain syndrome (7), and certain migraine syndromes (8), with each showing modest treatment responses to rTMS. In 2018, the United States Food and Drug Administration (FDA) approved marketing of TMS for the treatment of major depressive disorder, and in 2013, the FDA did the same for certain migraine headache types (9).

Pharmaceutical interventions with anti-epileptics, migraine therapies, and acetazolamide have historically been used to treat VS, and anecdotal evidence and/or limited treatment trials have shown very limited to no efficacy with side effects that often outweigh the benefits [for review of recent treatment data, see (4)]. Consequently, people with VS syndrome can suffer from decreased ability to read, to use a computer, or to drive, and they frequently report poor quality of life due to VS symptoms and anxiety associated with the syndrome (4). Transcranial magnetic stimulation (TMS) utilizes a non-invasive magnetic field to induce electrical currents that are directed at the cerebral cortex discretely, in order to alter neuronal firing. The rTMS method involves the use of continuous “trains” of stimulation for a specified duration of time, in order to produce lasting effects on brain function by either selectively increasing or decreasing neuronal firing. Repetitive TMS has improved outcomes in several neurologic and psychiatric disorders, including chronic tinnitus syndromes without hearing loss (10), which can, on some level, be considered analogous to the disorder of VS. Furthermore, many patients with VS suffer from chronic tinnitus (1, 2).

The goal of rTMS using low frequency (i.e., 1 Hz) stimulation is to decrease neuronal firing, and the inhibitory modulation likely occurs at the level of the synapse, although additional understanding is needed (11). A single pulse of TMS can alter neuronal firing at the moment the pulse is delivered. However, for longer-lasting effects that go beyond the moment of stimulation, repetitive stimulation with 5–20 daily sessions are typically necessary for longer-lasting effects, and 10 sessions have been found to be effective in a variety of disorders [see Table 2 and (12)].

**Table 2 T2:** Summary of data reviewed by Lefaucheur et al. (12).

**Summary of the tables within Lefaucheur et al. (12)**	**Range of pulses per session**	**Range of sessions (one session per 24 h unless noted)**	**Level of evidence (level 1: randomized sham trial through level 4: case series or uncontrolled)**
Table 1. HF-rTMS of M1 contralateral to pain region in neuropathic pain.	1,500–3,000	3–10	2
Table 2. HF-rTMS of bilateral M1 regions in Parkinson's disease (motor symptoms).	600–1,000	5–10	2
Table 3. LF-rTMS of contralesional M1 in motor stroke at the postacute stage.	900–1,800	5–15	2–3
Table 4. HF-rTMS of ipsilesional M1 in motor stroke at the postacute stage.	500–1,350	5–10	2
Table 5. iTBS of ipsilesional M1 in motor stroke at the chronic stage.	600–1,200	10	2, 3
Table 6. HF-rTMS of ipsilesional M1 in post-stroke dysphagia.	500–3,000	5–10	2, 3
Table 7. LF-rTMS of right IFG in post-stroke non-fluent aphasia at chronic stage.	600–1,200	10–20	2, 3
Table 8. rTMS (cTBS) studies in hemispatial neglect (target: left posterior parietal cortex).	4cTBS trains of 15–45 min	2–14	2, 3
Table 9. iTBS of M1 in multiple sclerosis.	600–1,200	10	2
Table 10. LF-rTMS of the auditory cortex in chronic tinnitus.	900–2,000	10 with some mixed (e.g., 4 sessions x 1,800 and 5 sessions x 1,200 pulses)	1, 2, 3
Table 11. LF-rTMS of the auditory cortex combined with HF-rTMS of the left DLPFC in chronic tinnitus.	1,000–2,000	5–10	1, 2
Table 12. HF-rTMS of the left DLPFC in major depressive disorder.	1,600–2,100	10–20 (one study with two sessions in 1 day)	1, 2, 3
Table 13. Deep HF-rTMS of the left DLPFC in major depressive disorder.	1,980–6,012	20	1, 2
Table 14. cTBS/iTBS of the right/left DLPFC in major depressive disorder.	600–1,800	10–30	2, 3
Table 15. LF-rTMS of the left TPC in auditory hallucinations (schizophrenia).	1,000–1,200	4 (two sessions per day)	2
Table 16. HF-rTMS of the left TPJ in auditory hallucinations (schizophrenia).	2,600	4 (two sessions per day)	2
Table 17. HF-rTMS studies of the left DLPFC in negative symptoms of schizophrenia.	1,000–1,500	10–15	1, 2, 3
Table 18. LF-rTMS of the DLPFC in obsessive compulsive disorder.	1,200–2,000	10–15	2, 3
Table 19. Bilateral LF-rTMS of the pre-SMA in obsessive compulsive disorder.	1,200–1,500	18–25	2, 3

*LF, Low Frequency; HF, High Frequency. cTBS, continuous patterned rTMS; iTBS, intermittent patterned rTMS brain stimulation; Note: this VS study protocol uses LF-rTMS, which depresses hyperexcitable neurons, which HF-rTMS activates neuronal activity*.

The mechanism causing more persistent change in neuronal activity is thought to be due to “weakening” of synaptic connections and synaptic plasticity that follows multiple sessions, but the mechanism is not fully understood (11). One theory posits persistent post-synaptic change (i.e., remodeling of the post-synaptic receptor) takes place only after multiple rTMS sessions with many stimulations given per session. These changes at the synaptic level appear to be akin to a physiologic process called long-term depression, or LTD, which can reduce cortical excitability and contribute to cortical plasticity and to learning and memory (13).

Evidence-based guidelines and therapeutic approaches for the use of rTMS in various conditions have been published and recently updated by Lefaucheur et al. in February 10 (12). Those reviewed in detail by Lefaucheur et al. are summarized in Table 2.

To date, there is no published data regarding the use of TMS for the treatment of VS. The goals for publishing the protocol for the ongoing study are to stimulate interest and to share approaches with the scientific community, as well as review the challenges encountered thus far. The methods and the TMS protocol are reviewed, followed by discussion of recruitment during COVID-19, as well as the challenges encountered and potential solutions that could inform planning for future rTMS treatment trials for VS.

## Methods and Analysis

The ongoing study is an open-label feasibility treatment study of VS utilizing a rTMS paradigm. In summary, participants undergo a 2-week treatment intervention for a total of 10 sessions that are ~1 h in duration per session and occur 5 days per week for two consecutive weeks. Assessments described are given at baseline (pre-treatment), post-treatment, and again at 1 and 3 months following treatment.

### Description of Population Being Enrolled

Up to 10 participants ranging in age from 19 to 65 with a diagnosis of VS that meets the International Headache Society (IHS) criteria are being recruited.

Inclusion Criteria:

Age 19–65 years with a diagnosis of VS that meets IHS criteriaAble to provide informed consentVisual snow must be present for 3 months or more and symptoms must be persistent (i.e., continuous)A prior brain magnetic resonance imaging (MRI) scan with and without contrast completed in the past 3 years that does not show signs of clinically significant brain lesion(s) (e.g., no evidence of multiple sclerosis, stroke, brain tumor, cortical heterotopia or other cortical developmental abnormalities, arteriovenous malformation, etc.).

Exclusion Criteria based on TMS safety guidelines (14–16):

Syndrome meeting criteria for Hallucinogen-persisting perception disorderPrior treatment with TMS for any disorderEpilepsy, family history of epilepsy, or personal history of seizuresAny medical condition or medication that increases the risk of seizuresPacemaker or another implantable medical deviceMetal in the skull, not including the mouthUnstable cardiac, pulmonary, or other systemic illnessPregnancyBipolar disorderHistory of suicidality.

### Outcome Measures

#### Questionnaires and Scales

Currently, no outcome measures or scales exist specifically for VS symptoms. For this reason, the CVSS was developed for this study, and is available as Supplementary Material. Additionally, two previously validated scales are being used: The National Eye Institute Visual Functioning Questionnaire—25 (VFQ-25) and the General Anxiety Disorder—7 (GAD-7) scale.

#### Psychophysical Visual Processing Tasks

Recently, McKendrick et al. (17) investigated psychophysical behavioral measures in people with VS compared to controls and found that VS participants showed statistically significant reduced center-surround contrast suppression and elevated luminance increment threshold detection in noise. These findings are consistent with the theory of cortical hyperexcitability. These tasks are, therefore, being employed in this feasibility study to investigate their use as potential markers of treatment efficacy.

The tasks detect extensively studied physiological properties of the visual system that have been used to explore the “balance between inhibition and excitation” and are described elsewhere (17, 18). In brief, for the center-surround matching task, observers are asked to compare the contrast between two small striped patches that are presented side-by-side. The “reference patch” is 40% contrast and is surround by a larger annulus of 95% contrast. The variable contrast small “target patch” is presented alone. Using a spatial forced-choice paradigm, participants must choose which patch is perceived as higher contrast. The strength of the influence of the surround annulus on the perception of the central patch contrast is a measure of the degree of center-surround suppression for each observer. The higher contrast surround (i.e., annulus) should suppress the perceived contrast of the central patch. The magnitude of this suppression of perceived contrast has been noted to be reduced in people with VS (17). For the luminance noise task, two squares filled with luminance noise are presented side-by-side and an observer must report which of the two stimuli also contains a circular luminance increment. Both high noise and low noise squares are used, and the luminance detection threshold is determined for each observer for each noise level. As noted, those with VS have been found to have a higher luminance detection threshold for luminance increments presented on both low and higher pixelated noise backgrounds (17). Learning effects were examined by McKendrick et al. (18) and were not found. The third task measures the ability to determine the global motion direction of a briefly presented field of moving dots presented within a circular window. Within the dot motion movie, some of the dots move in a coherent direction (either left or right, selected at random on each trial), while the remaining dots move in random directions (noise dots). On each trial, the observer indicates the perceived direction of global motion, with the threshold being measured as percent coherence (the percentage of dots in the pattern moving in the signal direction to correctly perceive the direction of motion). Full details of the thresholding methodology are presented elsewhere (18). This task did not show a difference between controls and participants with VS (17).

### Transcranial Magnetic Stimulation: Determining Phosphene Threshold

As described by Stewart and colleagues (19), the phosphene threshold is used to determine the personalized “dose” of TMS that will be used for each subject. The phosphene threshold is the “dose” of TMS that is necessary to result in the perception of phosphenes as described. For this study, this is done before the first TMS treatment and determined again at the start of week 2 (or treatment session 6) of the 10-session treatment schedule. To determine the phosphene threshold, participants wear a blindfold and a cap is worn on the head. Three points positioned over the occipital midline and 2, 3, and 4 cm above the inion are marked. The TMS coil is positioned such that the handle points upwards and is parallel to the subject's spine. Single pulse TMS is then applied over one of the marked points and the subject reports the presence or absence of a phosphene immediately after stimulation. Stimulation is initially applied at 60% of stimulator output. If the subject reliably perceives a phosphene, reporting it five or more times out of ten, intensity is reduced in steps of 5% and stimulation will be again given ten times. Stimulation intensity is reduced until the subject no longer reliably perceives a phosphene. Stimulation intensity is then increased in blocks of 5% until the minimum intensity at which the subject can perceive a phosphene five times out of 10 is established and this value is determined to be the threshold. If the participant does not initially perceive a phosphene at 60% of stimulator output, intensity is increased in blocks of 5% to a maximum level of 100% of stimulator output. If the subject fails to perceive a phosphene at the maximum level, the coil position is shifted to another of the points marked on the cap and the procedure will be repeated until the threshold is determined at one of the marked points.

### Transcranial Magnetic Stimulation: Treatment Procedure

For treatment in this pilot study, bilateral low-frequency (1 Hz) repetitive transcranial magnetic stimulation (LF-rTMS) is administered to both right and left lingual gyri using a custom-built, 120°-angulated, 80 mm double figure-of-eight coil manufactured by Magstim Ltd (Whitland, Camarthenshire, UK). Targets are selected based on visual inspection of a participant's T1-weighted MRI images of the brain, and individual target coordinates are recorded in Montreal Neurological Institute (MNI) space. The TMS coil is positioned over the specified target location based upon the participant's MRI image in MNI space facilitated by the Brainsight™ interface, and LF-rTMS is administered at 110% of the phosphene threshold using the determined target and trajectory. Treatment sessions include two 15–20 min trains (one train per side) for a total of no more than 1,800 stimulations during each treatment session. Each session includes a total of 30–40 min of LF-rTMS stimulation time with a brief break in between sides. For each session, after treatment is complete, the participant is given a side effect survey. The rTMS treatment sessions occur daily for 5 days per week for two consecutive weeks.

### Data Analysis

#### Side Effects

To determine whether any participant experiences untoward effects of TMS, a side effect survey is being used, as noted, and summary reports of adverse events will be published. It should be known that the cortical location of the treatment for this trial is different from previous studies, so it is possible to encounter side-effects not previously reported.

#### Drop-Out Rate Estimates

With a sample size of 10, we will be able to estimate the expected drop-out rate for larger studies in the range of 20–50% to within a 95% confidence interval of ±25% to ±31%. To calculate a dropout rate for future studies and shrink the confidence interval, we will use data gathered in this study and data from chronic tinnitus studies using TMS to perform a Bayesian analysis for drop-out estimation. For reference, the available studies [see (12)] for tinnitus and rTMS revealed an approximate dropout rate of 7% in rTMS group and 12% in the sham group.

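### The stated drop-out precision of ±25 to ±31 points matches a normal approximation that is unreliable at 10 participants, and it omits the low rates the plan itself cites

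*Protocol article*

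**What the plan says.** The Introduction of the protocol article lists the drop-out rate in the first of three specific aims. The statistical content of that aim is in Data Analysis, Drop-Out Rate Estimates. It begins "With a sample size of 10, we will be able to estimate the expected drop-out rate" and puts the precision for larger studies "in the range of 20–50% to within a 95% confidence interval of ±25% to ±31" percent. It does not say which interval method produced these figures.

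The same paragraph then plans to combine this study's data with "data from chronic tinnitus studies using TMS to perform a Bayesian analysis for drop-out estimation", with the purpose of narrowing the interval. For reference, it adds that the available tinnitus studies "revealed an approximate dropout rate of 7% in rTMS group and 12% in the sham group". It gives no reason for stating precision over 20–50% when both of these rates lie below 20%.

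The sample size of 10 is a ceiling: the population section says "Up to 10 participants ranging in age from 19 to 65".

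**The concern.** A symmetric plus-or-minus figure for a proportion from 10 people suggests the simple normal approximation, which behaves poorly when the expected number of events is small. If that is the source, the printed error bars are too optimistic on the upper side at low drop-out rates. The upper side matters most here, because the estimate is meant to inform larger studies and a drop-out allowance set too low leaves a trial short of participants.

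The second issue is the range. If drop-out resembles the cited tinnitus rates, the observed count will probably be 0 or 1. The precision sentence does not cover those results, and the approximation is at its worst there.

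**Working it through.** **Inputs.** n = 10, 95% level (taken as two-sided), rates of 20% to 50% and half-widths of 25 and 31 points, all from Drop-Out Rate Estimates. Reference rates of 7% and 12% come from the same paragraph.

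**Step 1: reproduce the plan's figure.** Wald half-width = 1.96 × √(p(1 − p)/n).
- p = 0.20: 1.96 × √(0.16/10) = 0.248, or ±25 points.
- p = 0.50: 1.96 × √(0.25/10) = 0.310, or ±31 points.

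Both ends match. The alternatives tried do not match both: Wald with continuity correction (29.8 and 36.0), t with 9 degrees of freedom (28.6 and 35.8), Wilson (22.7 and 26.3), and the mean Clopper-Pearson half-width (26.5 and 31.3; its upper end alone agrees). The method is therefore inferred, but the match is close.

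**Step 2: compare with exact intervals at n = 10.** Clopper-Pearson limits are the 2.5% quantile of Beta(x, n − x + 1) and the 97.5% quantile of Beta(x + 1, n − x).

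| Drop-outs | Wald 95% | Exact 95% | Exact distance below / above estimate (points) |
|---|---|---|---|
| 0/10 | 0 to 0% | 0 to 30.8% | 0 / 30.8 |
| 1/10 | -8.6 to 28.6% | 0.3 to 44.5% | 9.7 / 34.5 |
| 2/10 | -4.8 to 44.8% | 2.5 to 55.6% | 17.5 / 35.6 |
| 3/10 | 1.6 to 58.4% | 6.7 to 65.2% | 23.3 / 35.2 |
| 4/10 | 9.6 to 70.4% | 12.2 to 73.8% | 27.8 / 33.8 |
| 5/10 | 19.0 to 81.0% | 18.7 to 81.3% | 31.3 / 31.3 |

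At 2/10 the upper limit is understated by 55.6 − 44.8 = 10.8 points, and the Wald lower limit is impossible. At 5/10 the difference is 0.3 points.

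**Step 3: coverage of the Wald interval.** Sum the binomial(10, p) probabilities of the counts whose interval contains p.
- True rate 20%: 88.6%; 30%: 84.0%; 40%: 89.9%; 50%: 89.1%.
- On a fine grid over 20–50%: 79.0% to 95.0%, mean 89.6%.
- At the reference rates: 51.2% at 7% and 71.8% at 12%.

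**Step 4: what the reference rates imply for 10 participants.**
- Expected drop-outs: 10 × 0.07 = 0.7 and 10 × 0.12 = 1.2.
- P(0 of 10): 0.93^10 = 48.4% and 0.88^10 = 27.9%.
- P(0 or 1 of 10): 0.93^10 + 10 × 0.07 × 0.93^9 = 84.8%, and 0.88^10 + 10 × 0.12 × 0.88^9 = 65.8%.

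At either rate, the more likely result is an observed proportion below the range for which precision is stated.

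**The case against.** The strongest reply is that nothing was miscalculated. The figures reproduce, they are close to exact at 50%, and at 20% the mean exact half-width (26.5) is not far from 25. The message that 10 people give very poor precision is correct. This stands, and it limits the point to asymmetry and coverage, mainly at the low end.

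Several stronger readings are tempting, and the document does not support them:

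- **That a Wald interval will be reported.** The sentence is a planning statement and names no reporting method. The one analysis named for the drop-out rate is Bayesian. The coverage figures above describe the approximation behind the stated precision, not a committed analysis. Those at 7% and 12% also lie outside the range the sentence claims to cover.
- **That 20–50% contradicts 7% and 12%.** The tinnitus rates come from another condition and are offered for reference. The article itself describes work and travel burdens that could make a pessimistic range sensible. This is an unexplained mismatch, not a contradiction.
- **That the Bayesian step would return the tinnitus rate whatever this study shows.** That would need a prior size and a full weight that the article does not give. Such details may properly sit in the full protocol or analysis plan.
- **That enrolment will fall well short.** The precision sentence is conditional on 10. Recruitment difficulty is disclosed, and the Summary reports renewed interest. No particular smaller number can be taken from the text.
- **That any better method looks worse.** Wilson half-widths (22.7 at 2/10, 26.3 at 5/10) are narrower than those printed.

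**Conclusion.** The precision sentence needs a minor correction. On the inference that it uses the Wald formula, it attaches a 95% label to intervals with actual coverage of 84% to 90% at true rates of 20, 30, 40 and 50%. At 2/10 it shows ±25 points where the exact distances are -17.5 and +35.6. The fault fades as the rate approaches 50%. The sentence is also silent on rates below 20%, where both cited figures lie. There, 0/10 is a realistic result, for which the Wald interval has zero width and the exact one reaches 31%.

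The weight is limited. This is an open-label feasibility study, and the article ties no decision threshold or test to this interval. Any reader given the observed count can compute the exact limits.

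**What to change.** Replace the ±25 to ±31 statement with exact (Clopper-Pearson) 95% intervals for 10 participants: 0/10, 0–31%; 1/10, 0.3–45%; 2/10, 2.5–56%; 3/10, 7–65%; 4/10, 12–74%; 5/10, 19–81%. This covers both the 20–50% range and the lower reference rates, so the choice of range no longer needs defending. Add that 10 is the maximum enrolment, so these are best-case figures. State that the exact interval from the visual snow participants alone will be reported beside the planned Bayesian estimate.

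The cost is text only, with no change to conduct or data collection. The stated precision becomes slightly less favourable. Exact intervals are also conservative: their coverage at true rates of 20 to 50% is about 98% to 99%.
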